### Intervention

Both groups will follow a multidisciplinary team-based PR model at CHBV delivered by a pulmonologist, a physiotherapist and a nurse, and will include supervised exercise sessions and education and psychosocial support sessions in a group setting over a 12-week period. Other healthcare professionals, including a psychologist and a nutritionist will be involved in coordinating education and psychosocial support sessions.

#### Exercise sessions

The exercise sessions will follow the same structure for both groups and will be delivered in accordance with international guidelines [35, 37, 38]. It will occur twice per week for a maximum of 90 min. Continuous telemetry with electrocardiogram and oxygen saturation will be used and perceived dyspnoea and fatigue will be monitored with modified Borg scale throughout the session [39]. Intensity of the aerobic and resistance training will be prescribed using the 6-min walking test (6-MWT) or the cardiopulmonary exercise testing (if available) and the one-repetition maximum (1-RM), respectively. Exercise sessions will include 10 min of warm up, 30 to 40 min of aerobic cycle ergometer and/or treadmill training at 80% of the average speed achieved during the 6-MWT or 60% of their work peak [37, 40], 20 to 30 min of resistance training at 60 to 70% of 1-RM [37], and 10 min of cool down. Progression of training intensity will be tailored according to the perceived dyspnoea and fatigue (4–6 in the modified Borg scale) [39]. Adjunct components such as airway clearance techniques, balance training, inspiratory muscles training and electric neuromuscular electrical stimulation will be prescribed according to individuals’ needs within this timeframe.

#### Education and psychosocial support sessions

The education and psychosocial support sessions will follow the same structure for both groups, however the number of sessions will be different, and the content areas will sometimes vary, as described below.

Each education and psychosocial support session will be delivered after the exercise training and will last approximately 60 min. Family and/or friend caregivers will be invited and encouraged to take part in all sessions. They will be led by healthcare professionals of the multidisciplinary team and all participants will sit in a circular arrangement. An interactive style will be followed, to engage people with COPD or ILD and their family and/or friend caregivers in an active dialogue and reflection about the topic being discussed. The healthcare professional will avoid medical jargon and facilitate participation of the group e.g., asking open questions that lead to meaningful interaction. An active effort will be conducted to adapt the education process to the characteristics of participants at an individual level e.g., revising topics covered at the end to confirm the achievement of the core knowledge and skills. Moreover, written materials will be provided at the end of each session.

##### Sessions dedicated to both groups

The following topics will be explored in both groups (i.e., EG and CG): a) information on chronic respiratory diseases; b) medication, inhaler techniques, oxygen therapy and non-invasive ventilation; c) symptom management and exacerbations; d) exercise and physical activity; e) action plan; f) anxiety and depression management; and g) nutrition.

##### Sessions dedicated only to the experimental group

For the EG there will be four additional face-to-face sessions: a palliative care session, a “Peer-to-peer session” and two “Get-apart sessions” (i.e., one dedicated exclusively to people with COPD or ILD and another one dedicated exclusively to their family and/or friend caregivers); and online sessions, within the 12-week period.

In “Peer-to-peer session” and “Get-apart sessions” the focus will be to discuss participants’ own issues with the multidisciplinary team but opinions about how to optimize PR for them will also be gathered. Moreover, every two weeks and for approximately 40 min, people with COPD or ILD and their family and/or friend caregivers will have the opportunity to discuss any health-related issues with a healthcare professional from the multidisciplinary team via zoom platform (i.e., online sessions). These sessions will be individualized according to participants learning needs and perspectives identified during PR. Moreover, participants that cannot attend to face-to-face sessions will have this opportunity to discuss the most relevant information to manage their disease.

Individual cases from both groups will also be referred for evaluation by a specialist palliative care team or by any other health and social care professional (e.g., psychologist or social worker) according to the specific unmet needs identified.

##### Education session on palliative care

The education session on palliative care will be facilitated by two healthcare professionals, a medical doctor and a nurse, both specialized in the field. The main topics that will be discussed are presented in Table 1. A written leaflet summarizing the main information about palliative care will be given to people with COPD or ILD and their family and/or friend caregivers.

**Table 1 Tab1:** Description of the education session on palliative care delivered during pulmonary rehabilitation to people with chronic obstructive pulmonary disease or interstitial lung diseases and their family and/or friend caregivers

Content areas	Discussion topics
Palliative care	Concept/definition of palliative care Role and goals of palliative care
Symptom control	Dyspnoea (including dyspnoea crisis), fatigue, cough and anorexia management
Impact of the disease	Impact of the disease on individual and family and/or friend caregiver Maintaining a balance between hope and fears
Psychosocial support	Hospital- and community-based resources
Planning for the future	Advance care planning

##### “Peer-to-peer session” and “Get-apart sessions”

People with COPD or ILD and their family and/or friend caregivers will be the primary communicators in the “Peer-to-peer session”, and the dialogue will be based on participants suggestions. This session will provide participants with an opportunity to share their knowledge, competences and experiences, listen to other people living with the same disease, and to some extent give and receive support from peers. In the week before, people with COPD or ILD will receive a total of nine cards with printed statements corresponding to the Patient Reported Experience Measure in Chronic Obstructive Pulmonary Disease (PREM-C9) [41] items. People will be asked to select one or two cards of most important personal meaning and value, and the session will be initiated talking about the statements’ themes. This strategy will capture some possible topics that people with COPD or ILD would like to discuss, prioritize content, as well as promote participant engagement.

In the “Get-apart sessions”, people with COPD or ILD will have the opportunity to discuss their issues apart from their family and/or friend caregivers and vice versa. This can be particularly helpful for people who feel more reluctant, ashamed or even stigmatized to reveal private concerns, doubts and thoughts in front of their loved ones. Both the “Peer-to-peer session” and “Get-apart sessions” will be supervised by healthcare professionals from the multidisciplinary team.

#### Referral of individual cases to the specialist palliative care team

Participants from both groups might be referred to the specialist palliative care team by the pulmonologist of the PR program, who has interest and basic training in the field. The decision will be taken after considering the input of all members of the multidisciplinary team and the holistic assessment of the person with COPD or ILD and the family and/or friend caregiver. Multiple aspects will be considered such as symptom severity, indicators of clinical deterioration, functional status decline and respiratory function, as well as family and/or friend caregiver’ needs [18, 22, 42]. People with COPD or ILD and family and/or friend caregivers who manifest willingness to be evaluated by a specialist palliative care team will also be referred. Participants might be referred at any time point during the intervention, and such decision (refer or not refer) will carefully be reviewed at the end of PR.

### Baseline assessments

Quantitative data will be collected from all participants at baseline

The following data will be collected from people with COPD or ILD through self-report, healthcare records and direct measurements: a) sociodemographic information (i.e., age, sex, educational level, marital and employment status); b) health status [smoking status, comorbidity(ies), medication, oxygen treatment, non-invasive ventilation and exacerbation(s), hospital admission(s) and fall(s) within the last 12 months]; c) health literacy (European Health Literacy Survey in Portuguese, HLS-EU-PT) [43]; d) cognitive status (six-item cognitive impairment test, 6CIT) [44]; e) anthropometry [height and weight to calculate the body mass index (BMI)]; and f) respiratory function [residual volume (RV), total lung capacity (TLC), RV/TLC ratio, pre and post bronchodilator forced expiratory volume in the first second (FEV_1_) and forced vital capacity (FVC), and diffusing capacity for carbon monoxide (DLCO)].

Family and/or friend caregivers will provide information on their: a) sociodemographics (i.e., age, sex, educational level, marital and employment status); b) health status [disease(s), limitation(s) in activities of daily living, medication and fall(s) within the last 12 months]; c) health literacy (HLS-EU-PT); d) cognitive status (6CIT); and e) role of caring [relationship with the care receiver, additional help (if any) from other co-caregiver(s), caregiver tasks and amount of time performing these tasks, length of caring, geographical distance to the care receiver house, and single vs multiple care receiver(s) at once].

### Outcomes

The primary outcome will be knowledge about palliative care evaluated with the Palliative Care Knowledge Scale (PaCKS) [45]. Data will be collected at baseline (T0) and end of PR (T1). At 6-months post-PR (T2), only patient-reported outcome measures will be collected. Table 2 provides a detailed description of primary and secondary outcomes that will be assessed throughout the study period. Some outcomes, such as functional capacity, peripheral muscle strength and balance are not expected to be influenced by education, however they are important to assess the effectiveness of PR delivery.

**Table 2 Tab2:** Overview of outcomes and outcome measures evaluated in people with chronic obstructive pulmonary disease or interstitial lung diseases and their family and/or friend caregivers

Outcome	Outcome measure	Description	MCID^a^	People with COPD or ILD	Family and/or friend caregivers	T0	T1	T2
Knowledge about palliative care	PaCKS [45]	- Self-reported questionnaire with 13 items which are true or false. A broad range of topics are assessed, including goals, target population and timing of palliative care, as well as symptoms and problems that palliative care addresses - For each statement, “True”, “False” and “I don’t know” options are provided, and a mark is given for each correct answer - Scores range from 0/13 to 13/13, with higher scores indicating higher knowledge	Not applicable	⬤	⬤	×	×	×
Attitude towards palliative care referral	“Would you like (your loved one) to be referred to a specialist palliative care team at this time?” [46]	- “Would you like to be referred to a specialist palliative care team at this time?” and “Would you like your loved one to be referred to a specialist palliative care team at this time?” will be asked to people with COPD or ILD and their family and/or friend caregivers, respectively - Possible answers are “Yes”, “No” or “Don’t know”	Not applicable	⬤	⬤	×	×	×
	“Would you like (your loved one) to be referred to a specialist palliative care team if your (your loved one’) health deteriorates?”	- “Would you like to be referred to a specialist palliative care team if your health deteriorates?” and “Would you like your loved one to be referred to a specialist palliative care team if your loved one’ health deteriorates?” will be asked to people with COPD or ILD and their family and/or friend caregivers, respectively who do not answer "Yes" to the previous question - Possible answers are “Yes”, “No” or “Don’t know”	Not applicable	⬤	⬤	×	×	×
Pain	“Do you feel pain?” Pain charts [47] and VAS [48, 49]	- Participants will be asked about pain perception with a closed question: “Do you feel pain?” - In affirmative cases, pain charts and VAS will be used to identify its location and to measure its intensity, respectively - Scores will be recorded on a 10 centimeters (cm) line that represents a continuum between “no pain” and “worst pain”	VAS -1.37 cm	⬤	⬤	×	×	×
Dyspnoea	mMRC [50, 51]	- 5-point scale graded from 0 (“No breathlessness except on strenuous exercise”) to 4 (“Too breathless to leave the house or breathless when dressing or undressing”). Higher scores indicate greater dyspnoea severity on daily activities	-1 grade	⬤		×	×	×
Fatigue	FACIT-FS [52, 53]	- 13-item questionnaire assessing tiredness, weakness, listlessness, lack of energy, and their impact on HRQoL - Each item is rated from 0 (“Not at all”) to 4 (“Very much”). Total score ranges from 0 to 52. Higher scores indicate less fatigue	+ 4.7 points	⬤	⬤	×	×	×
Cough	LCQ [54, 55]	- 19-item questionnaire containing three domains: physical, psychological and social - Each item is rated from 1 to 7. Final score ranges from 3 to 21. Higher scores indicate weaker influence of cough on quality of life	+ 1.3 points	⬤		×	×	×
Anxiety and depression	HADS [56, 57]	- 14 multiple-choice items divided into 7 item subscales for anxiety (HADS-A) and depression (HADS-D) - Scores in each subscale range from 0 to 21. Higher scores indicate greater levels of anxiety and/or depression. Clinically significant anxiety or depression are interpreted by scores ≥ 8	HADS-A -1.5 points HADS-D -1.5 points	⬤	⬤	×	×	×
Disease impact	CAT [58, 59]	- 8-item questionnaire which addresses cough, sputum, chest tightness, dyspnoea, home daily activities, confidence leaving home, sleep and energy levels in a 6-point scale rated from 0 to 5 - Score ranges from 0 to 40. Higher scores indicate more severe impairment on health status. A score of more than 20 indicates high impact	-2 points	⬤		×	×	×
HRQoL	SGRQ [60, 61]	- 50-item questionnaire which evaluates three different domains contributing to overall health, daily life, and perceived well-being: symptoms, activity and impact - A score in each domain and a total score are calculated and weighted, ranging from 0 to 100. Higher scores indicate worse HRQoL	-4 points	⬤		×	×	×
Needs	SNAP [62, 63]	- 15 questions with the format: “Do you need more support with…” (e.g., “Do you need more support with managing your symptoms?”) - For each statement, “No”, “A little more” and “Quite a bit more” options are provided to identify the domains in need of support - There is an optional additional open-ended question to capture “anything else” not already covered - The final question refers to the caregiver needs: “Does a family member or friend who helps you need more support?”	Not applicable	⬤		×	×	×
	CSNAT [64, 65]	- 14 questions covering caregivers’ broad support domains which fall into two distinct groups: support that enable them to provide care and more direct personal support for themselves - All questions follow the format: “Do you need more support with…” (e.g., “Do you need more support with knowing what to expect in the future?”) - For each question, “No”, “A little more”, “Quite a bit more” and “Very much more” options are provided to identify support needed within any of the domains - There is an optional additional open-ended question to capture “anything else” not already covered	Not applicable		⬤	×	×	×
Functional performance	LCADL [66, 67]	- 15 activities of daily living organized in four domains: self-care, domestic, physical and leisure - Each item is rated from 0 (“I wouldn’t do it anyway”) to 5 (“I need someone else to do this”), except for one additional question on global impact with “A lot”, “A little” and “Not at all” as answer choices - Final score ranges from 0 to 75. Higher scores indicate greater functional limitation	LCADL -3 points LCADL % of total -4 points	⬤		×	×	×
Functional capacity	6-MWT [68, 69]	- Evaluates the distance walked at a fast pace during 6 min in a 30 meters (m) corridor	+ 30 m	⬤		×	×	
Peripheral muscle strength	Quadriceps strength 1-RM [37, 70] Handgrip strength HHD [71, 72]	- Quadriceps strength, 1-RM: determines the greatest amount of weight in kilogram (kg) that the participant could move in a double leg extension manoeuvre (isotonic strength) - Handgrip strength, HHD: measures the maximum isometric strength of the hand and forearm muscles at the dominant side in kg	Quadriceps + 5.7 kg, 26.9% Handgrip Not available	⬤		×	×	
Balance	Brief-BESTest [73, 74]	- 8-item scale evaluating 6 domains contributing to postural control in standing and walking: biomechanical constraints, stability limits/verticality, transitions/anticipatory postural adjustments, reactive postural control, sensory orientation and stability gait - Each domain is evaluated with a test scored from 0 (severe impairment) to 3 (no impairment), with a maximum of 24. Higher scores indicate better balance performance	+ 3 points	⬤		×	×	
Knowledge about COPD	BCKD [18]	- 65 statements divided in 13 topics, each with a stem; these topics cover epidemiology and physiology, aetiology, common symptoms, breathlessness, phlegm, chest infections, exercise, smoking, immunization, inhaled bronchodilators, antibiotics, and oral/inhaled steroids - For each statement, “True”, “False” and “I don’t know” options are provided, and a mark is given for each correct answer - Total score corresponds to the percentage of correct answers	Not available	⬤	⬤	×	×	×
Burden of providing care	ZBI [75]	- 22-item questionnaire addressing impact of caring experience in several domains: health and wellbeing, personal and social life, and finances - Each question has five response options rated from 0 (“Never”) to 4 (“Almost always”), except for the final question on global burden, rated from 0 (“Not at all”) to 4 (“Extremely”). Final score ranges from 0 to 88. Higher scores indicate greater burden. A score of more than 24 indicates high burden	Not available		⬤	×	×	×
Adherence	-	- Number of attended exercise sessions and education and psychosocial support sessions	Not applicable	⬤	⬤		×	
Adverse events	-	- Occurrence of adverse events during PR	Not applicable	⬤			×	
Referral to a specialist palliative care team	-	- Number of people with COPD or ILD referred to a specialist palliative care team	Not applicable	⬤			×	×

The symbol ⬤ identifies the outcomes to be assessed in people with chronic obstructive pulmonary disease or interstitial lung diseases and/or their caregivers. The symbol × identifies the outcomes to be assessed in each timepoint (i.e., T0, T1 and T2)

*Legend—T0* Baseline, *T1* End of pulmonary rehabilitation, *T2* 6-months post-pulmonary rehabilitation, *1-RM* One-repetition maximum, *6-MWT* 6-min walking test, *BCKD* Bristol COPD Knowledge Questionnaire, *Brief-BESTest* Brief-Balance Evaluation Systems Test, *CAT* COPD Assessment Test, *COPD* Chronic obstructive pulmonary disease, *CSNAT* Carer Support Needs Assessment Tool, *FACIT-FS* Fatigue Functional Assessment of Chronic Illness Therapy-Fatigue Subscale, *HADS* Hospital Anxiety and Depression Scale, *HHD* Hand-held dynamometer, *HRQoL* Health-related quality of life, *ILD* Interstitial lung diseases, *LCADL* London Chest Activities of Daily Living, *LCQ* Leicester Cough Questionnaire, *MCID* Minimal clinically important difference, *mMRC* Modified Medical Research Council questionnaire, *PaCKS* Palliative Care Knowledge Scale, *PR* Pulmonary rehabilitation, *SGRQ* Saint George’s Respiratory Questionnaire, *SNAP* Support Needs Approach for Patients, *VAS* Visual analogue scale, *ZBI* Zarit Burden Interview

^a^The minimal clinically important differences (MCID) reported are based on data from people with chronic obstructive pulmonary disease, except the MCID of visual analogue scale (VAS) that is based on data from people with rheumatological diseases

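### The attitude question at T1 and T2 has no answer for people already referred, so their 'No' cannot be told apart from unwillingness

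*Protocol article*

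**What the plan says.** Table 2 (Methods, Outcomes) measures attitude towards palliative care referral with two linked questions, both marked for patients and caregivers at T0, T1 and T2. The first, in its patient form, is "Would you like to be referred to a specialist palliative care team at this time". The caregiver form asks the same about the loved one. The permitted answers are Yes, No and Don't know. The second question, "Would you like to be referred to a specialist palliative care team if your health deteriorates", goes to those "who do not answer 'Yes' to the previous question". Neither question has an exemption, a skip rule or an answer for someone already referred.

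The section on referral of individual cases to the specialist palliative care team applies to both arms. It says "Participants might be referred at any time point during the intervention", and that the decision is looked at again when rehabilitation ends. Referral follows a team assessment of several clinical and caregiver aspects. In addition, patients and caregivers "who manifest willingness to be evaluated by a specialist palliative care team will also be referred".

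The last row of Table 2 counts patients referred, at T1 and T2. The article does not link that count to the attitude answers.

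**The concern.** The referral rule acts on the attitude that the item measures. A participant who becomes willing may be referred before T1 or T2 and is then asked whether they would like to be referred now. 'No, because I already am' is a truthful answer, and the form records it exactly as it records a refusal. Don't know has the same problem.

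Two comparisons are exposed. Between arms, the Background hypothesises that the intervention will change attitude towards referral. If it raises willingness and so leads to more referral, the ambiguous answers gather in the experimental arm and the recorded difference shrinks. Over time, someone who says Yes at T0, is referred, and says No at T1 looks like a loss of interest. The item suits nearly all patients at T0, because the Participants section excludes those who had specialist palliative care in the previous 12 months. At T1 and T2 it covers a mixture of referred and unreferred people, so a change from baseline mixes attitude with referral status.

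**Working it through.** **1. The plan's own figures.** None is stated for the attitude outcome. The only sample size is for the PaCKS time-by-group interaction (two groups, two timepoints, alpha 0.05, f = 0.25, correlation 0.5). With noncentrality λ = N × 2 × f² / (1 − 0.5), N = 34 gives λ = 34 × 2 × 0.0625 / 0.5 = 8.5 on 1 and 32 degrees of freedom, and power 0.807. N = 32 gives 0.781. So 34 reproduces, and 34 / 0.6 = 56.7, which is 58 as two equal groups. This point changes none of it.

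**2. The two rules side by side.**
- Who is asked: all patients and caregivers, at T1 and T2, whatever their referral status.
- Who may already be referred by then: people in either arm, at any time during rehabilitation, including those who showed willingness.
- What they can answer: Yes, No or Don't know.
- What follows: any answer other than Yes leads to the question about future deterioration, which also takes no account of an existing referral.

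A referred person therefore has no answer that describes their position.

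**3. What that could do to a comparison (assumed figures).** Let p be the true proportion with a favourable attitude at T1, r the share of those already referred, and q the share of those referred who do not answer Yes. The recorded proportion answering Yes is p × (1 − r × q). Assume p = 50% in the experimental arm (EG) and 20% in the control arm (CG), 29 per arm and no dropout. Power is for a two-sided 5% normal test of two proportions with pooled variance under the null.

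| r in EG / CG | q | Yes recorded, EG v CG | Difference (points) | Power |
|---|---|---|---|---|
| 0 / 0 | any | 50% v 20% | 30 | 68% |
| 25% / 25% | 50% | 43.8% v 17.5% | 26.3 | 59% |
| 25% / 25% | 100% | 37.5% v 15% | 22.5 | 50% |
| 50% / 50% | 100% | 25% v 10% | 15 | 32% |
| 50% / 0 | 50% | 37.5% v 20% | 17.5 | 31% |
| 50% / 0 | 100% | 25% v 20% | 5 | 7% |

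For example, 0.50 × (1 − 0.25 × 1) = 0.375 and 0.20 × (1 − 0.25 × 1) = 0.15. When r × q is equal in both arms, the difference shrinks by the factor 1 − r × q and the ratio stays at 2.5. The largest loss needs referral to be concentrated in the experimental arm. With r = 0, or if every referred person still answers Yes (q = 0), nothing is lost. The documents give neither r nor q, so the table shows the mechanism and is not an estimate.

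**The case against.** A good deal can be said on the other side.

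- *No scoring rule is given.* The article does not call Yes the favourable outcome, does not dichotomise the answers and names a test only for the primary outcome. Classification can be left to an analysis plan. This stands, so nothing here says that the plan scores referred people as unwilling. But the wording, answer options and timepoints are fixed in Table 2, and an analysis plan cannot supply an answer that was never offered.
- *The gap is partly covered.* The second question gives a favourable person another chance to say so, and referrals are counted separately. This helps only in part. Wanting referral on deterioration fits a referred person no better, and the count is not tied to the answers.
- *Referred people may still say Yes.* True, and nothing in the article shows how they would answer.
- *Referral is not the same as willingness.* It also follows symptom severity, deterioration, functional decline, respiratory function and caregiver needs. Some referred people may be unwilling, and their No would be a real No. This stands, and it is why referral should not simply be counted as a favourable attitude.
- *The stakes are low.* Attitude is one of many secondary outcomes, under an aim to explore effects. This stands.

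A reader might infer that the comparison is necessarily biased to nothing, or reversed. The documents do not support that. In the illustration, with no control participant affected, the arms become equal only when r × q in the experimental arm reaches 1 − 0.20/0.50 = 0.6. No referral rate in the article suggests such a value.

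**Conclusion.** The point holds as a flaw in measurement. From T1 on, the item is put to people for whom it may no longer apply, and their No or Don't know cannot be separated from unwillingness. The missing answer option is certain from the text. Dilution between arms or over time is possible, and depends on three things that the article does not give: how many are referred before each questionnaire, whether this differs by arm, and how referred people answer. Under the assumed figures a true 30-point difference is recorded as anything from 30 down to 5 points, and the real loss could be nil. The effect is confined to this secondary outcome. It is worth correcting because the correction is cheap.

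**What to change.** At T1 and T2, add the answer 'already referred or followed by the specialist team' to the first question, in both the patient and the caregiver versions. Do not count it as No. Limit the second question to those who answer No or Don't know, since under the present routing the new answer would also lead there. Report attitude by arm for all randomised participants in four categories: Yes, No, Don't know and already referred.

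For answers already collected, use the patient referral status recorded at T1 and T2 to flag people already referred. It can also flag the caregiver item, which concerns the same patient, although it says nothing about the caregiver's own attitude. Check that the referral came before the questionnaire, because the decision is also reviewed at the end of rehabilitation.

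A composite that treats 'already referred with the participant's agreement' as favourable should be a sensitivity analysis at most. The article does not describe agreement as recorded. It would also put the decision of a programme clinician, who is not described as blinded, into a participant-reported outcome.

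The cost is a small change to one item while data collection is under way (it runs to June 2026), so earlier and later answers will have been given on slightly different forms. No extra visit is needed, and no change to the clinical referral rule is implied.

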**Methods:**

A randomized controlled study will compare PR with palliative care education (experimental) with traditional PR (control) in people with COPD or ILD and their family and/or friend caregivers. Family and/or friend caregivers will be invited to take part in education and psychosocial support sessions. In addition to the usual educational content, the experimental group will have a session on palliative care, a “Peer-to-peer session”, two “Get-apart sessions” and online sessions. The “Peer-to-peer session” and the “Get-apart sessions” will be discussions about topics suggested by participants. The “Get-apart sessions” will be dedicated to people with COPD or ILD apart from their family and/or friend caregivers and vice versa. The online sessions will be zoom meetings to discuss any health-related issues raised by participants, at a flexible time. A mixed-methods approach will be used to evaluate the outcomes. The primary outcome will be knowledge about palliative care. Secondary outcomes will include attitude towards palliative care referral, symptoms, disease impact, health-related quality of life, needs, knowledge about the disease, burden of providing care, adherence, adverse events and referral to a specialist palliative care team. Quantitative and qualitative data will be collected at baseline and end of PR. At 6-months post-PR, only patient-reported outcomes will be collected. For the primary outcome, time*group interaction will be analyzed with mixed analysis of variance.

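### Adherence is defined as a count of attended sessions, but the experimental arm is offered more education sessions, so equal attendance gives unequal counts

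*Protocol article*

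**What the plan says.** The Methods paragraph of the abstract includes adherence among the secondary outcomes ("burden of providing care, adherence, adverse events and referral to a specialist palliative care team"). Table 2, in the Outcomes section, gives its measure as "Number of attended exercise sessions and education and psychosocial support sessions", recorded at the end of rehabilitation for both patients and caregivers. The row mentions no percentage, no number of sessions offered and no restriction to particular sessions.

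The section Education and psychosocial support sessions says that the two arms share a structure, "however the number of sessions will be different". The section on sessions for the experimental group only adds: "For the EG there will be four additional face-to-face sessions". These are a palliative care session, a peer-to-peer session and two get-apart sessions, the last being "one dedicated exclusively to people with COPD or ILD and another one dedicated exclusively to their family and/or friend caregivers". The same section gives this arm online meetings: "every two weeks and for approximately 40 min, people with COPD or ILD and their family and/or friend caregivers will have the opportunity".

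Exercise sessions have the same structure in both arms and take place twice a week. The programme lasts 12 weeks.

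**The concern.** A count of sessions attended can be read as adherence only if everyone compared was offered the same number. Here the number offered differs by arm, by design, in the education and support component. The count then mixes two things: how much was scheduled and how faithfully people came.

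Two misreadings could follow. Equal adherence would look like better adherence in the experimental arm. A fall in attendance at the shared sessions, which is worth detecting when an intervention adds sessions to a programme, could be masked by attendance at the added ones.

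**Working it through.** The article gives no figure for adherence and no total of sessions offered per arm, so there is no stated result to reproduce. The sample size calculation concerns the primary outcome and does not enter.

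**Inputs from the article**
- Extra face-to-face sessions per person in the experimental arm: 1 palliative care + 1 peer-to-peer + 1 get-apart = 3. Four are held, but each get-apart session is closed to the other type of participant.
- Online sessions in the experimental arm: one every 2 weeks over 12 weeks, 12 / 2 = about 6. The article does not say whether they count towards adherence, so both 0 and 6 are used.
- Exercise sessions: 2 × 12 = about 24 in each arm.

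**Assumptions**
- Number of common education sessions, C. The article lists seven topics, not a number of sessions. C = 7 (one per topic) and C = 14 are shown.
- The same attendance rate r in both arms and for all session types; r = 60%, 80% and 100% are shown.

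**Difference in education counts**

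Expected count = r × sessions offered, so the difference is r × (C + 3 + online) − r × C = r × (3 + online). C cancels.

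| r | Online not counted | Online counted |
|---|---|---|
| 60% | 0.6 × 3 = 1.8 | 0.6 × 9 = 5.4 |
| 80% | 0.8 × 3 = 2.4 | 0.8 × 9 = 7.2 |
| 100% | 3 | 9 |

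**Ratio of counts, experimental to control**

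Here r cancels, but C matters. The combined count adds 24 exercise sessions to each arm.

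| C | Education, online not counted | Education, online counted | Combined, online not counted | Combined, online counted |
|---|---|---|---|---|
| 7 | 10/7 = 1.43 | 16/7 = 2.29 | 34/31 = 1.10 | 40/31 = 1.29 |
| 14 | 17/14 = 1.21 | 23/14 = 1.64 | 41/38 = 1.08 | 47/38 = 1.24 |

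**The same count from different adherence**

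With C = 7, a control participant attending 80% has 0.8 × 7 = 5.6 sessions. An experimental participant reaches 5.6 by attending 5.6/10 = 56% of the face-to-face sessions, or 5.6/16 = 35% if the online sessions count.

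**Masking, by a constructed example**

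Take C = 7 and control attendance of 80%, a count of 5.6. Suppose the experimental arm attends 50% of the common sessions (3.5) and 80% of its three extra face-to-face sessions (2.4). Its count is 3.5 + 2.4 = 5.9. A fall of 30 percentage points at the shared sessions appears as slightly better adherence. This shows what the measure can hide; nothing in the article suggests that it will happen.

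**As a proportion**

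With attended/offered, equal attendance gives equal values, for example 80% and 80%, a difference of 0 whatever the schedule.

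**The case against.** The strongest reply is that no comparison of adherence between arms is planned in this document. The Statistical analysis plan section specifies an experimental-versus-control comparison only for the primary outcome, and adherence appears in neither the hypotheses nor the aims. That is correct and limits the consequence. Even so, a randomised trial that lists an outcome as secondary and records it in both arms invites the reader to compare them.

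A second reply is that Table 2 is an overview in a condensed article, and that dividing by sessions offered may be left to a fuller document. That would answer a missing detail. Here the table positively states a count, while in other rows it says so when a percentage is meant, as for the COPD knowledge score. A fuller document may add a proportion, but the published definition would still conflict with the unequal schedule.

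A third reply is that the exercise half of the measure is sound. This stands: both arms are offered about 24 sessions. If the two components are reported separately, the exercise count can be compared as it is. For patients, a combined count dilutes the distortion to a ratio of 1.08 to 1.29. Caregivers have little of this offset, because the abstract invites them to the education and support sessions and their measure lies mainly there.

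A fourth reply is that the upper figures depend on counting the online sessions. These are shorter and individualised, and also serve people who cannot attend in person, so they may not be meant to count. This also stands, and is why the lower figures are given. The direction does not depend on it.

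Two stronger readings are tempting and are not supported. A reader might infer that the count favours the experimental arm whatever happens. It does so at equal attendance; with C = 7 and online sessions not counted, experimental attendance below 56% against 80% in the control arm would reverse it. A reader might also infer that education denominators differ between patients and caregivers within an arm. They do not: each person in the experimental arm is offered three extra face-to-face sessions.

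**Conclusion.** The point holds for the education and support count and for any count that combines it with exercise. At equal attendance the experimental arm's count is higher by 1.8 to 5.4 sessions at 60% and by 2.4 to 7.2 at 80%, whatever the number of common sessions. The lower end rests only on the three extra sessions that the article states; the upper end also counts about six online sessions. The relative size, 1.43 to 2.29 with 7 common sessions or 1.21 to 1.64 with 14, rests on an assumed number of common sessions.

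The exercise count alone is not affected, and neither is the primary outcome. This is a badly fixed secondary measure that should be corrected before analysis; it does not threaten the trial's main conclusion.

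**What to change.** Amend the adherence row of Table 2 as follows:

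- Define adherence as sessions attended divided by sessions offered, separately for exercise and for education and support.
- Make any comparison between arms only on sessions offered to both arms: exercise and the common education sessions.
- Report attendance at the palliative care, peer-to-peer, get-apart and online sessions within the experimental arm, as intervention exposure.
- State whether online sessions count, and whether one that replaces a missed face-to-face session counts as attendance at that session.
- State the number of common education sessions.

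The cost is a few lines of text. The intervention, sample size and visits do not change. The article does not describe how attendance is recorded; counting attended sessions implies some record, and the only added requirement is that it identifies the type of session. This should be confirmed now, since recruitment began in August 2023 and data collection is expected to end in June 2026.
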